## 1.2 OBJECTIVES

### 1.2.1 Primary objectives

The primary objective of this study is to evaluate the effectiveness of a multicomponent intervention (MCI) programme (physical activity [PA], nutritional counselling/dietary intervention, and information & communication technology [ICT] intervention) compared with a healthy aging lifestyle education (HALE) programme on the hazard rate of mobility disability assessed by the inability to complete a 400-m walk test in less than 15 minutes without sitting, help from another person or use of a walker, in non-disabled older people with physical frailty and sarcopenia (PF&S).

### 1.2.2 Secondary objectives

The secondary objectives are to evaluate the effect of the MCI programme compared with the HALE programme on relevant health-related outcomes, in particular:

- Changes in physical performance measures,
- Changes in disability status,
- Changes in body composition, anthropometric and nutritional measures,
- Changes in cognitive function and mood,
- Incidence of falls and injurious falls
- Modifications of quality of life
- Difference in use of healthcare services
- Difference in mortality

A cost-effectiveness analysis is also planned and will be conducted by a dedicated team within work package 5.

### 1.3 DETERMINATION OF SAMPLE SIZE

The sample size calculation was based on the LIFE-M study database ([1](#), [2](#)). Specifically, survival analyses were run according to different levels of Short Physical Performance Battery (SPPB) score (lower than 8, versus 8 and 9). The outcome considered was major mobility disability (i.e. inability to complete the 400-m walk test). The effect of PA on major mobility disability was negligible in participants with a baseline SPPB score  $\geq 8$  (hazard ratio=0.94; 95% confidence interval [CI]: 0.72-1.23;  $p=0.65$ ). Conversely, the hazard ratio was statistically significant in participants with a baseline SPPB score lower than 8 (hazard ratio=0.75; 95%CI: 0.59-0.94;  $p=0.012$ ).

- A sample of 1,200 older persons with SPPB score  $< 8$  enrolled over 12 months is estimated to provide 85% power (434 events) to detect a 25% reduction in the hazard of major mobility disability over a maximum of 36 months of follow-up, considering an exponential dropout rate of 25% over 2 years and a log rank test with a 5% two-sided alpha level. An interim blinded sample size reassessment after 11 months from the beginning of recruitment allows taking immediate actions to preserve the study power in case the efficiency of enrolment or the number of observed events is not coherent with the original assumptions.
- In addition to not restrict the enrolment to older people with SPPB score lower than 8 that would jeopardize the aim of project to comprehensively characterize the PF&S condition and to not decrease the study power hence, the probability of success of the trial, it was decided to include in the study a convenience sample of 300 older adults with baseline SPPB score 8 or 9. An ad hoc hierarchical testing procedure has been formulated to control type I error: first, we will compare the effects of the

interventions in participants with SPPB score lower than 8 and, only in case of significant result (i.e., two sided  $p < 5\%$ ), the comparison will be extended to the whole study population

- At the first blinded sample size reassessment (may 2017) it was decided to increase the accrual period by 6 months, but maintaining a maximum of 36 months of follow-up period
- The last participant was randomized on November 15th 2017 (1205 in SPPB<8 stratum, 314 in SPPB 8-9 stratum)
- A second blinded power reassessment was performed on May 7th 2018, and revealed a lower than expected number of events (215 vs. 270). Therefore, in order to maximize the probability to reach the requested number of event (434) at the end of the study, the study duration has been increased by 7 months.

#### 1.4 STUDY PLAN

Approximately 1500 participants will be randomized in a ratio 1:1 to the following two treatment groups:

- HALE programme (n = 750 ; approximately n=600 with SPPB<8 and n=150 with SPPB≥8)
- MCI programme (n = 750 ; approximately n=600 with SPPB<8 and n=150 with SPPB≥8))

In the MCI intervention group, the PA component is designed to be performed both at the center and at home. Participants will train at the center twice a week under direct supervision of instructors. The PA schedule below shows the expectation in term of center-based sessions and home-based exercises.

**Table 1 – Intervention staff contacts for the PA group**

| Week                               | Center-based PA | Home-based PA                                                                 |
|-------------------------------------------|------------------------|--------------------------------------------------------------------------------------|
| Adoption (week 1-52)                      | 2 times each week      | 1time/week (week 1-4)
2 times/week (week 4-8)
Up to 3-4 times/week (week 8-52) |
| Maintenance (weeks 53 – end of the trial) | 2 times each week      | Up to 3-4 times/week                                                                 |

| Week | Center-based PA | Home-based PA |
|------|-----------------|---------------|
|------|-----------------|---------------|

The total amount of PA has to be monitored by investigators using results of actimetry from the ActivPAL™ device (measured at baseline and every 6 months [ $\pm 2$  weeks]). In addition, the local dietician/nutritionist (D/N) will train each participant randomized to the MCI group on how to complete a 3-day dietary record. The 3-day dietary record will be collected from each participant in the MCI intervention group at baseline and every 12 months. This assessment will then support the elaboration of personalized nutritional recommendations by the local D/N, in agreement with national and international guidelines.

In the HALE programme arm, participants will meet in small groups, two times per month with required participation at least one per month. The HALE programme is based on workshop series, during which participants receive information on a variety of topics of relevance to older adults. At the end of the class, there is also 5-10 minutes of instructor-led programme of upper extremity stretching exercises or some relaxation techniques.

The participants will have a different length of follow-up according to the date of his/her recruitment. Those randomised at the beginning of the recruitment phase will have a longer follow-up duration (up to 3 years) compared with those included at the end of recruitment (minimum 2 years of follow-up).

The study flow chart of the administration of questionnaires and measures according to the clinic visits scheduled is detailed in section 7 of the protocol.

## 1.5 MODIFICATIONS TO THE STATISTICAL SECTION OF THE PROTOCOL

This section summarizes major changes to the protocol statistical section with emphasis on changes after study start (after the first participant was enrolled).

The statistical section of the protocol was not changed in an amendment

## 1.6 STATISTICAL MODIFICATIONS MADE IN THE STATISTICAL ANALYSIS PLAN

Not applicable

## 2 STATISTICAL AND ANALYTICAL PROCEDURES

### 2.1 ANALYSIS ENDPOINTS

#### 2.1.1 Demographic and baseline characteristics

The baseline value is defined as the last available value up to the randomization visit V1 – T0 or date of randomization if V1 is missing (included).

All baseline safety and efficacy parameters (apart from those listed below) are presented along with the on-study summary statistics in the safety and efficacy sections ([Section 2.4.5](#) and [Section 2.4.4](#)).

##### *Demographic characteristics*

Demographic variables are gender (Male, Female), race (White, Black or African American, Asian, American Indian or Alaska Native, Native Hawaiian or other Pacific Island, Other), age in years (quantitative and qualitative variable : <70, [70 – 75[, [75 – 80[, [80 – 85[, [85 – 90[, ≥ 90), ethnicity (Hispanic or Latino, Not Hispanic or Latino, Not reported, Unknown), and country. In addition to demographic variables, height, weight and BMI (quantitative and qualitative variable : <18.5, [18.5 – 25[, [25 – 30[, [30 – 35[, [35 – 40[, ≥ 40) will be presented as baseline characteristics.

##### *Medical or surgical history*

Medical history and medical findings include:

Physical examination (normal/abnormal/exclusion): skin, lungs, heart, extremities, neurological System, vascular system (present/absent).

Medical (or surgical) histories (Y/N/Refused/Don't know):

- Any cardiovascular medical history: High blood pressure or hypertension; heart attack, or coronary, or myocardial infarction leading to overnight hospitalization; heart failure or congestive heart failure; angina or chest pain due to blockages in the arteries of the heart; coronary artery bypass surgery; stent and/or angioplasty of the coronary arteries; carotid endarterectomy; pacemaker
- Any diabetes medical history: Diabetes, sugar in urine, or high blood sugar; oral antidiabetic drugs intake; use of insulin injections
- Any neurologic medical history: transient ischemic attack (TIA) or mini-stroke ; stroke or brain hemorrhage leading to hospitalization ; difficulty from the stroke (Arm and/or leg still weak/hard to use, Trouble walking, Trouble with speech and/or Other)

- Any cancer or malignant tumor, excluding minor skin cancer
- Any musculoskeletal medical history: broken or fractured hip leading to hospitalization, other broken or fractures bones since the age of 50 (wrist/arm/back or spine/other bones);
- Any arthritis medical history during the last 6 months: arthritis or rheumatism; any pain and/or stiffness in the joints (hands or fingers/shoulders/knees/hips/back or spine/foot)
- Any cirrhosis or liver disease
- Any chronic lung disease (chronic bronchitis, COPD, asthma, or emphysema)
- Any emotional, nervous or psychiatric problems, since the age of 50
- Any fall over the past year and number of times (1-3 times/4 or more falls), injurious falls requiring doctor, emergency room, hospital or urgent care center in past year
- Other predefined medical history in the 5 past years inquiry from physician or medical professional advice regarding: back injury, paralysis, fainting or passing out, shortness of breath, asthma, chest congestion/cough, abnormal heart rhythm, depression, foot ulcer, a wound that would not heal
- Any symptoms in the past 6 months of: anxiety, fatigue, decreased appetite, insomnia, dizziness, muscle or joint stiffness, muscle strain or soreness, sprain (ankle or knee), foot pain
- Any other medical conditions that might affect ability to participate in a physical activity program
- Other medical and surgical history in the last 5 years: this information will be coded using the version of Medical Dictionary for Regulatory Activities (MedDRA) currently in effect at Sanofi at the time of database lock.

### ***Disease characteristics at baseline***

Specific disease history includes:

- The SARC-F total score range from 0: best to 10: worst (quantitative and qualitative variable: <3, 3, 4, ≥ 5). A score equal to or greater than 4 is predictive of sarcopenia.
- The 400-meter walk test duration at baseline (min) and 400-m walk speed (m/s), (see details in [Section 2.5.2](#)),

- The local and central reading of the Appendicular lean mass (aLM) (kg) and aLMBMI (Body mass index-adjusted appendicular lean mass) by gender assessed by Dual energy X- ray absorptiometry (DXA). Discrepancies between local and central readings assessed by aLM >0.5 or <-0.5 kg or delta aLMBMI > 0.05 or <-0.05 will be summarized by categories
- The SPPB total score (quantitative and qualitative variable: <8, ≥ 8; scale from 0: low performance to 12: high performance)
- The Mini Mental State Examination (MMSE) total score (scale from 0: severe cognitive impairment to 30: normal cognitive function)
- The Cumulative Illness Rating Scale (CIRS): Total score, severity index and comorbidity index.

Any technical details related to computation are described in Section 2.5.

### 2.1.2 Prior or concomitant medications

All medications taken by the participants during the screening visit and for each subsequent visits all medications taken in the past two previous weeks before the visit, including ATC coded medications and non ATC coded medications, are to be reported in the case report form pages.

All ATC coded medications will be coded using the World Health Organization-Drug Dictionary (WHO-DD) using the version currently in effect at Sanofi at the time of database lock.

- Prior medications are those the participant reported at the screening visit. Prior medications can be discontinued before the first intervention or can be ongoing during the study.
- Concomitant medications are any treatments reported by the participant at any post-randomization visits (i.e. from V2-Month 3).

### 2.1.3 Efficacy endpoints

The observation period of efficacy data is from the randomization visit V1-T0 or date of randomization if V1 is missing (excluded) until the end of the study.

Except the 400-meter walk tests, all measurements, scheduled or withdrawal visit (V9), will be assigned to analysis windows defined in Section 2.5.4 in order to provide an assessment of the efficacy parameters for Month 3 to Month 36 time points.

The baseline value is the last available and valid measurement obtained up to the randomization visit V1-T0 or date of randomization if V1 is missing (included).

### 2.1.3.1 Primary efficacy endpoint(s)

The primary endpoint is the time (in days) from randomization to the date of first occurrence of major mobility disability assessed by the inability to complete the 400-meter walk test within 15 minutes, without sitting, help from another person or use of a walker.

This time is calculated as date of event minus date of randomization visit V1-T0 (or date of randomization if V1 is missing) + 1 day.

The 400-meter walk test is assessed at Month 3 then every 6 months after the randomization visit.

#### **Adjudication of primary endpoint**

All 400-meter walk tests not performed (including missing tests due to visits performed by phone or proxy) will be adjudicated. A pre-defined algorithm will be applied to automatically adjudicate the missing tests (i.e. disability ascertained or no disability). Following this automatic adjudication, all remaining missing tests will be then evaluated by an adjudication committee.

The algorithm was built by identifying all the information recorded in the eCRF that was related to the participants' walking ability. Once selected, all this information (e.g. answers to questionnaires, results from the gait speed test, etc.) was then included in a logistic regression model run on all available 400-meter walk tests in order to determine which information was most predictive of the disability status (i.e. success or failure).

To adopt a conservative approach, the selected information was then fine-tuned to limit the number of tests wrongly classified as no disability to 5%. The number of tests wrongly classified as disability reaches 25%.

The resulting algorithm, based on result from the Gait speed test and some answers obtained from the ADL Proxy and Assistive Device questionnaires, is as follows:

1. "Disability ascertained" if:

- Gait speed test performed in 0.4 m/s or less **OR** participants not able to walk the 4 meters **OR** had to use an aid other than a cane to walk
- **OR** participants answer "Yes" to at least one of the following questions:
  - *"When the subject walks outside his/her home, does he/she usually require a walker?"*
  - *"When the subject walks outside his/her home, does he/she usually require a tripod or a quad cane?"*
  - *"When the subject walks inside his/her home, does he/she usually require a walker?"*
  - *"When the subject walks inside his/her home, does he/she usually require a tripod or a quad cane?"*

- **OR** participants answers “*Unable to do*” or “*A lot of difficulty*” to at least one of the following questions:
    - “*Walking for 400 metres, which is a little shorter than half a kilometre?*”
    - “*Walking for more than one kilometre because of your health?*”
  - **OR** participants answers “*Unable to do*” or “*A lot of difficulty*” or “*Some difficulty*” to the question “*Walking 100 metres because of your health?*”
2. “No disability” if:
- Gait speed test performed in more than 0.67 m/s (less than 6 sec to walk 4 meters) without an aid other than a cane **OR** Lawton ADL score equal to 8
  - **AND** participants answer “*No difficulty*” to the 2 following questions
    - “*Walking for 400 metres, which is a little shorter than half a kilometre?*”
    - “*Walking 100 metres because of your health?*”
  - **AND** participants answer “*No difficulty*” or “*A little difficulty*” or “*Some difficulty*” to the question “*Walking for more than one kilometre because of your health?*”

Then, the adjudication committee will assess remaining missing 400-m walk tests using all information in the following available eCRF modules:

- 400-meter walk test
- Assistive device questionnaire
- PAT-D
- ADL Proxy
- Outcome events
- Adverse events

The 3 possible assessments by the adjudication committee are “Disability ascertained”, “No disability” or “Disability not conclusive” (i.e. when the outcome could not be adjudicated due to the lack of available information)

### **Derivation of primary endpoint**

Disability will be considered ascertained:

- at the date of the 400-meter walk test, if participants fail to walk 400 meters within 15 minutes, or need an assistive device
- or at the date of the visit (or date of the 400-meter walk test if available) when the visit is performed but the participant did not perform the 400-meter walk test and the adjudication (automatic or from the committee) does not classified the event as no disability (i.e. ascertained or not conclusive) if any

- or at the date of death if the participants died during the study

Participants who have not met this disability criterion at the end of their study participation (including withdrawals) will be considered as right-censored observations. The censoring time will be calculated as the date of their last successful completed 400-meter walk test (including assessment of “no disability” by the automatic adjudication or the adjudication committee) minus the date of randomization visit V1-T0 (or date of randomization if V1 is missing) + 1 day.

**Particular cases:** In the case where more than 9 months are observed between two consecutive visits or between the last available visit and the death:

- If the disability criterion is not met at the 2nd consecutive visit, then participants will be censored at the date of their first consecutive visit. In the case where the first of the two consecutive visits is the randomization visit, then the censoring time will be equal to 1.
- If the disability criterion is observed at the 2nd visit of the two consecutive visits, or the participant died more than 9 month after the last available visit, then the disability will be considered ascertained at the date of the first consecutive visit or at the date of the last available visit before to die, plus 183 days (i.e., 6 months). In the case where the first of the two consecutive visits (or the last available visit before to die) is the randomization visit, then the disability will be considered ascertained at the date of randomization visit V1-T0 (or date of randomization if V1 is missing) + 183 days.

If no post-baseline visit is done, then participants will be censored at the date of randomization visit V1-T0 (or date of randomization if V1 is missing).

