#### **4.2.2. Primary outcome**

In agreement with what already tested in the LIFE study, the SPRINTT consortium has selected the 400-metre walk test as the primary outcome measure for the full-scale trial time to the onset of major mobility disability. The objective component of the major mobility disability outcome is defined as the inability to complete a 400-metre walk test within 15 minutes, without sitting, help from another person or use of a walker. Individuals who require more than 15 minutes to complete the walk have an extremely slow pace (<0.45 m/sec), which would make their walking capacity of little utility in daily life. Selecting a higher cut-point, such as 30 or 60 minutes, makes the objective assessment impractical and does not add to the clinical significance of the outcome.

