### 7.3.1. 400 Meter Walk Test

The 400-m walk test will be assessed using standardised conditions. A 20-m track will be marked using colour cones. Participants will be asked to walk 400 metres at their usual pace and without overexerting themselves. During testing, they may not use any assistive devices (except for a cane). Subjects will be instructed to begin the test at the start line from a standing position, to walk down the corridor, turn around the cone in a continuous loop, and repeat the course 10 times to complete the 400-metre walk. After each lap, the observer will announce the number of laps completed and the number remaining. During the walk, if participants feel the need to stop and rest, they will be allowed to stand in one place and rest without sitting. They will be instructed to resume walking as soon as they will be able to do so. If they will be unable to continue after a 60-second rest stop or if they need to sit down, the test will be stopped. There will be no limits to the number of allowable rest stops, as long as the participant can complete the walk within 15 minutes without sitting. The test will be discontinued after 15 minutes, a time that corresponds to a very slow walking speed (0.45 m/s), and that translates into a walking capacity that has little utility in daily life. Participants unable to complete the test within 15 minutes will be considered to be mobility disabled. Heart rate will be recorded at the beginning and end of the test. The number, timing, and reasons for the rest stops (fatigue, chest pain, feeling faint or dizzy, shortness of breath, or other) will be recorded. The inability to complete the 400-metre walk has already been used as the defining criterion for mobility disability in major clinical studies, in particular the LIFE pilot and full-scale trials.

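### As written, the SAP rule for performed 400-metre walks makes needing any assistive device a primary event, with no exception for the cane that the protocol allows

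*Combined protocol and SAP*

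**What the plan says.** The endpoint definition names one device, a walker. Protocol 4.2.2 has "inability to complete a 400-metre walk test within 15 minutes, without sitting, help from another person or use of a walker", and SAP 2.1.3.1 has "inability to complete the 400-meter walk test within 15 minutes, without sitting, help from another person or use of a walker". Eligibility (protocol 5.1.2.2) likewise rules out only a walker at the baseline walk.

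Protocol 7.3.1 sets the test procedure: "During testing, they may not use any assistive devices (except for a cane"). Protocol 7.3.2 also allows a cane in the SPPB gait test.

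For a performed walk, the SAP's Derivation of primary endpoint dates the event at the test "if participants fail to walk 400 meters within 15 minutes, or need an assistive device". No device is named or exempted.

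For a walk that was not performed, the SAP's automatic adjudication does exempt a cane in the 4-metre gait test. Disability is ascertained if the participant "had to use an aid other than a cane to walk", and the no-disability rule accepts an adequate gait speed achieved "without an aid other than a cane". The same algorithm counts a usual need for some canes as disability: "does he/she usually require a tripod or a quad cane".

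SAP 1.5 and 1.6 record no change to the statistical methods, so no deliberate departure from the protocol is documented.

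**The concern.** The derivation bullet turns test results into event dates. The protocol's wording makes a cane an assistive device, though a permitted one. A participant who entered the trial walking with a cane could repeat the same walk in the same time at Month 3, the first follow-up test, and meet the event rule as it reads.

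Such events would say nothing about the intervention. Randomisation should spread them evenly, so the expected result is dilution of the hazard ratio towards 1 and loss of power, not an advantage to one arm. They would also count towards the 434 events that SAP 1.3 uses to set the study's length.

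The rules would also be inconsistent with one another:

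- **Missing tests.** A cane user could be an event when the walk is done, and be classed as not disabled when it is missed and the other no-disability criteria are met.
- **Persistent mobility disability (SAP 2.1.3.2).** This endpoint has no device clause for performed tests, so one cane-assisted walk could be a primary event without being a failure there.
- **Supportive analysis (SAP 2.4.4.1).** It removes only deaths, so no planned analysis would reveal the problem.

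**Working it through.** **1. The rules side by side**

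| Place | Devices that disqualify | Ordinary cane |
|---|---|---|
| Protocol 4.2.2, primary outcome | Walker | Not named |
| Protocol 5.1.2.2, baseline walk | Walker | Not named |
| Protocol 7.3.1, test procedure | Any assistive device but a cane | Allowed |
| SAP 2.1.3.1, endpoint definition | Walker | Not named |
| SAP adjudication, gait test in missing walks | Any aid but a cane | Exempt |
| SAP adjudication, usual aids | Walker, tripod cane, quad cane | Not named |
| SAP derivation, performed walks | Any assistive device | No exception |

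Only the last row, read literally, makes an ordinary cane an event.

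**2. The planned figure**

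Inputs from protocol 10.1 and 7.4.3.2: hazard ratio 0.75, two-sided alpha 0.05, power 85%, allocation 1:1. By Schoenfeld's formula:

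events = 4(1.960 + 1.036)² / (ln 0.75)² = 434.

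This reproduces the stated 434. Power at 434 events is 85.0%.

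**3. Size under the literal reading**

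The share *c* of cane users is not in the documents, so 2–20% is shown as an assumption. Suppose that all cane users become events at Month 3, equally in both arms, and that they would otherwise have had the same event rate as everyone else. With the planned 1,200 participants with SPPB <8:

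- events without effect = 1,200*c*
- events carrying the effect = 434(1 − *c*)
- observed ln HR = ln 0.75 × 434(1 − *c*) / [434(1 − *c*) + 1,200*c*]
- power = Φ(½ × √(total events) × |ln HR| − 1.960)

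For *c* = 5%: 60 and 412.3 events, total 472.3. Then ln HR = −0.2877 × 412.3/472.3 = −0.251, HR = 0.778 and power = Φ(10.87 × 0.251 − 1.960) = 77.9%.

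A log-rank simulation checked this (1,500 runs per scenario; 12-month accrual, 36-month study, exponential dropout of 25% over 2 years).

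| Assumed cane users | Added events | HR, formula | Power, formula | HR, simulated | Power, simulated |
|---|---|---|---|---|---|
| 0% | 0 | 0.750 | 85.0% | 0.751 | 84.9% |
| 2% | 24 | 0.762 | 82.3% | not run | not run |
| 5% | 60 | 0.778 | 77.9% | 0.777 | 77.2% |
| 10% | 120 | 0.802 | 70.1% | 0.796 | 71.7% |
| 20% | 240 | 0.844 | 54.0% | 0.824 | 60.9% |

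With an explicit cane exception, the planned figures of 434 events and 85% power are unchanged.

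**The case against.** The strongest reply is that the bullet is shorthand. The same SAP section has just defined the endpoint as completion "without sitting, help from another person or use of a walker", and a walk with a cane is a valid test under protocol 7.3.1. Read together, the bullet would mean a device that the test does not allow, and needing a device may be narrower than using one. The adjudication algorithm lends some support. It was built from a regression on the success or failure of available walks, yet it exempts an ordinary cane. Had cane walks been coded as failures, a cane should have predicted failure. This is inference, but it makes the benign meaning plausible.

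It does not make the text safe. Where the SAP wants a cane exemption it writes one, and the bullet has none. Two programmers could derive different event counts from it.

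A reader might go further in three ways that the documents do not support:

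- **That eligible cane users will be counted as events.** No code or eCRF specification is shown.
- **That a large effect is established.** The share of cane users is unknown. The event counts with Fig S2 (SPPB 8–9) show no early burst: cumulative events in the first three columns are 0, 1, 9 and 0, 0, 4 among 155 and 159 participants. The column times cannot be read from the available text, and this is the fitter, non-primary stratum, so the counts do not settle the matter for SPPB <8.
- **That a walk finished with another person's help escapes counting**, because the bullet does not mention help. The bullet does not mention sitting either. The endpoint definition in the same section disqualifies both.

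**Conclusion.** Wrong as written. The event rule for performed walks conflicts with the endpoint it implements, with the test procedure, and with the SAP's own handling of missing walks. That conflict is on the page and depends on no assumption.

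The consequence is conditional. It requires that the rule was applied literally and that a material share of participants with SPPB <8 walked with a cane. If 5–10% did, the hazard ratio would move from 0.75 to about 0.78–0.80 and power from 85% to about 77–78% (at 5%) or 70–72% (at 10%). These figures assume equal cane use in both arms. Misclassification is a risk of the wording, not a shown result.

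**What to change.** Reword the first bullet of the SAP's Derivation of primary endpoint along these lines: the participant does not complete 400 m within 15 minutes, or sits, is helped by another person, or uses a walker or any other aid that protocol 7.3.1 does not allow, an ordinary cane being allowed.

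State how tripod and quad canes are classified in a performed walk, and reconcile this with the adjudication algorithm, which treats a usual need for one as disability. Apply the same device rule to performed and adjudicated tests. Use it also to define a successful test for censoring.

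Before database lock, check that the program follows the clarified rule and, if aid use was recorded, count the performed walks whose classification depends on a cane. The cost is a sentence or two in the SAP and the matching code. The planned sample size and event target do not change.
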